**Fig. 2 Fig2:**
[figure not shown]
Patient participant trial processes. *GP* General practitioner, *LBP* Low back pain

##### Inclusion/exclusion criteria

This study will include patients aged 18 years and over who present to a participating GP with LBP of any duration as their primary complaint. Patients will not be eligible if they have had back surgery in the last 6 months, have been unable to do their normal work (or normal daily activities for those who are retired, unemployed or work at home) for more than 3 of the last 6 months, have LBP due to a non-back-related condition (e.g., cauda equina compression, inflammatory arthritis, malignancy, infection, aortic stenosis or aneurysm), have a concomitant health condition which means they are not suitable for trial participation (e.g., pregnancy or major psychological disturbance), or are unable to read and write in English.

##### Informed consent

This trial complies with the Declaration of Helsinki and has received approval from the New Zealand Central Region Health and Disability Ethics Committee (16/CEN/43). Because the FREE approach is consistent with current best practice recommendations [28], patients do not need to consent to receive treatment with the approach itself. Patients will need to consent to being a research participant, but this process will not refer to the type of treatment they may receive. Eligible patients will receive a participant information sheet. Written informed consent will be obtained by a research nurse.

##### Concomitant care

Patient care concomitant to the FREE intervention will not be controlled or limited. It will be monitored through the Otago Costs and Consequences Questionnaire for Low Back Pain (OCC-Q-LBP).

### Participant retention

During the trial, contact will be maintained with practices by having a research nurse on site or on call during patient enrolment, as well as regular emails and monthly practice visits from the research team. Patients will be sent a voucher to acknowledge their participation in each questionnaire round. Vouchers will be delivered with the subsequent questionnaire (so that participants will receive a voucher at the same time as a questionnaire) to maximise responses [29, 30]. Methods of follow-up may include text message, email, telephone and social media [31], with participants consenting to follow up by one or more of these methods at enrolment. A website (www.lowbackpain.co.nz) will also be used to communicate with participants and for participants to advise researchers of changes to contact details. A further, optional consent will be obtained to follow participants for up to 5 years through subsequent surveys using the same instruments employed in the present study.

### Allocation arms

#### Intervention group

GPs in practices allocated to the intervention group will be trained in the FREE approach. The FREE approach to LBP was developed on the basis of a systematic review of the literature [32], in-depth interviews with GPs and people who had acute and chronic LBP [33–35], and a national survey [36]. These findings were synthesised with current research evidence on back pain, behaviour change and guideline implementation to create a novel approach. A full description of the development and basis of FREE is available elsewhere [26].

The FREE approach is a complex intervention which combines GP and patient belief change with behaviour change approaches. The aim of FREE is to optimise the behaviour of both GPs and patients and shift focus to factors and behaviours which have been shown to influence outcome while reducing the provision of unhelpful, threat-related information to patients.

Key GP behaviour change goals are (1) increased confidence to manage back pain and reduced GP anxiety related to screening for pathology; (2) increased understanding of the impact of psychosocial factors on patient outcomes, with tools for exploring and managing these factors; and (3) increased confidence that movement and activity are safe, with tools for demonstrating this confidence to patients. Key patient behaviour change goals are (1) reduced threat associated with LBP, (2) decreased fear of movement and decreased perceived need to protect the back, (3) improved expectation of outcome from a back pain episode, and (4) increased activity and work participation.

Additional file 2 describes the behaviour change techniques (BCTs) employed in FREE in relation to GPs. The BCTs employed for patients are presented in Additional file 3. These techniques are described using the BCT taxonomy developed by Michie et al. [37].

#### Control group

GPs within a practice allocated to the control group will receive no training during the intervention and follow-up periods, during which time they will continue to provide current usual care. This has been chosen as the comparator because it is the best care available locally outside the study. All GPs have access to current LBP treatment guidelines.

At the end of the trial, control group GPs will be offered an opportunity to attend the FREE workshop. This will provide comparable benefits for being part of a research trial.

### Randomisation, allocation concealment and blinding

#### Randomisation

General practices will be randomly assigned to either the intervention or control group (i.e., all GPs in a practice will be randomised to the same arm) with a 1:1 allocation, using a computer-generated randomisation schedule stratified by the number of FTE GPs within the practice (≤8 versus > 8 FTE). The aim of the stratification procedure is to ensure that approximately equal numbers of GPs are allocated to the intervention and control groups. An independent statistician will conduct the randomisation process. Analysis of outcomes will include this practice size stratification variable as a fixed effect to account for the impact of this design element on study results.

GP participants will be randomised by practice for the following two reasons: (1) Individual patient randomisation is not feasible, because GPs may find it difficult to provide ‘usual care’ after learning about the new approach, which would result in contamination of results from control patients; and (2) randomisation at the level of the individual GP (rather than practice) may result in contamination effects if intervention GPs discuss the FREE approach with control arm GPs within their practice.

#### Allocation concealment

All general practices participating in the trial (and GP participants currently working in these practices) will be recruited before group allocation occurs. GPs may leave and others may join these practices (and become eligible for the trial) during the period between randomisation and data collection. New GPs will be kept blinded to their practice’s group allocation until they have decided whether to participate in the trial (using the same information as their peers). An independent statistician at a central administration site will perform the randomisation. The independent statistician will communicate practice allocation to the primary investigator so that training may be planned in intervention practices and data collection dates can be agreed upon with all practices.

Patient recruitment will occur post-randomisation. All eligible patients will be invited to participate. Patients will be unaware of the trial’s existence and goals prior to presenting at the practice. Patients will also be unaware that two different treatment approaches are being compared within the trial, meaning that patient participants will be masked to cluster allocation. Research nurses at intervention and control group practices will use identical scripts and information sheets when approaching potential participants, screening participants for inclusion and explaining the study to minimise potential recruitment bias.

#### Blinding

The results dataset will be stored with the study arm identity blinded by way of a unique code for each study participant. The key to this code will be held (independent of the dataset for analysis) by the independent statistician, the chair of the data monitoring committee (DMC) and the principal investigator (PI). The PI needs to know practice group allocation to conduct the intervention group training workshops. The PI will not be involved in data collection, entry, modification or analysis.

Individual patients will remain blind to the presence of two study arms throughout the course of the trial. Consultation appearance will be similar from a patient perspective, except that intervention arm participants may be provided a FREE booklet and referred to the FREE website. Control arm participants may be given other informational materials (e.g., ACC pamphlet) or be referred to other information sites (e.g., patient.org). Even if a patient perceives he/she is receiving a different approach from previous GP LBP consultations, they will remain blind to the study hypothesis.

All patient participant data submitted on paper surveys will be entered or checked by a research assistant blind to group allocation. Data entered by participants through electronic surveys will be checked for completeness and anomalous responses.

Data cleaning and analysis will be conducted by the trial statistician who is blind to group allocation. Once analysis is complete, the results will be unblinded. To eliminate the risk that the trial statistician may have been inadvertently exposed to practice codes during the conduct of the trial, these will be replaced with new codes in the dataset prior to the trial statistician’s receiving the data. Only the independent statistician and the chair of the DMC will have access to the key for these new codes.

GPs and practices will necessarily be unblinded following group allocation because the need for training means GPs will know whether they are in the intervention or control arm prior to patient recruitment. GPs will be aware of their study allocation when completing baseline measures. This is necessary in order to minimise the time between completing baseline measures and receiving FREE training or starting patient recruitment. The content of the intervention will be unknown to all GPs at the time they complete their baseline questionnaire.

### Adverse events

The risks to participants in this trial are small, and no serious adverse events or side effects attributable to the treatment provided are expected. Patients and GPs will be encouraged to report all potential adverse events and incidents of serious pathology (and method of discovery) observed amongst trial participants to the research team on a continuous basis during the study, including through each follow-up survey. Adverse event reports will be reviewed by the DMC (detailed below).

### Data monitoring committee

The independent DMC includes an independent statistician, an independent senior researcher and an independent academic GP. The DMC will monitor aspects of the trial related to ethics, safety and data integrity. Because intervention efficacy analysis cannot be conducted until 6 months post-intervention and the total recruitment period is anticipated to be approximately 11 months, there will not be any potential for early termination of the study based on favourable or unfavourable results from interim analyses. Furthermore, cluster randomised trials are not suited to interim analysis because study power is contingent largely on the number of clusters (GPs) recruited at any point in time [38, 39]; given that this study will be recruiting patients from clusters (GPs) in sequence, there will not be sufficient data for interim analysis. Consequently, no interim analyses will be performed.

If serious adverse events are reported to the DMC which are unexpected and potentially related to the intervention, the DMC will be able to break the randomisation code to assess if the participant was part of the intervention or control group. The DMC will be able to provide this information to those providing health care to the participant and will determine whether there are grounds for stopping the trial early.

### Measures

Patient-related measures are presented in Fig. 3 (SPIRIT figure patient participants; further details in Additional file 4). GP-related measures are presented in Fig. 4 (SPIRIT figure GP participants; further details in Additional file 5). Patient data will be collected through surveys (electronic or postal); GP data will be collected through surveys (electronic or postal), research nurse audio recording of consultations and audit of clinical notes.

**Fig. 3 Fig3:**
[figure not shown]
Standard Protocol Items: Recommendations for Interventional Trials (SPIRIT) figure for patient participants. *Patient participants were assigned to intervention/control on the basis of allocation of the practice to which they presented (practices were randomized in this cluster randomized trial). ^†^Assessments completed prior to general practitioner consultation and intervention or control exposure. *RMDQ* Roland-Morris Disability Questionnaire, *NPRS* Numeric Pain Rating Scale, *NDRS* Numeric Disability Rating Scale, *EQ-5D* EuroQol five dimensions, *OCC-Q-LBP* Otago Costs and Consequences Questionnaire, *ACC* Accident Compensation Corporation, *FREE* Fear Reduction Exercised Early, *GP* General practitioner

**Fig. 4 Fig4:**
[figure not shown]
Standard Protocol Items: Recommendations for Interventional Trials (SPIRIT) figure for general practitioner participants. *General practitioners were enrolled between 4 weeks and 1 day pre-randomisation. ^†^Allocation occurred between 5 weeks and 33 weeks before training was received. ^‡^Time point when intervention group practices attended initial training workshops. ^§^Assessment completed by intervention group participants only. *FREE* Fear Reduction Exercised Early, *HC-PAIRS* Health Care Providers’ Pain and Impairment Relationship Scale, *Back-PAQ* Back Pain Attitudes Questionnaire

#### Patient self-reported outcomes

The primary patient-level outcome measure will be back-related functional impairment 6 months post-initial LBP consultation (interim data at 2 weeks, 6 weeks and 3 months), measured with the Roland-Morris Disability Questionnaire (RMDQ) [40]. Secondary patient outcomes are listed in Additional file 4. The RMDQ, Numeric Pain Rating Scale (NPRS), satisfaction questions [41, 42] and EuroQol five dimensions (EQ-5D) [43] are validated tools recommended as standardised outcome measures for LBP research [42, 44] which gather data for the three core outcome domains recommended for clinical trials of non-specific LBP: physical functioning (RMDQ), pain intensity (NPRS) and health-related quality of life (EQ-5D) [44].

#### Patient objective outcomes

Secondary objective outcomes are the number of days off from work, the number of days on restricted duties and the quantity of medication taken. These will be self-reported by the patient and collected with the OCC-Q-LBP [45]. Cost-of-care data independently collected by ACC as part of standard back pain claim processing will be used to conduct a sensitivity analysis of OCC-Q-LBP data.

#### Patient-reported process measures

To examine the mechanisms by which FREE might impact patient outcomes, we will collect several patient-reported measures of pain and psychosocial function [46–51] (Additional file 4). These are modifiable factors known to be predictive of disability outcomes for LBP, and they form the targets of the FREE approach (*see* Additional file 3). These measures are collected for use as covariates for adjusting main outcome analysis and to inform mediation analysis [52]. Some questions have been modified for consistency (use of first person in questions for self-report, and Likert scales all set to a 7-point range).

#### GP self-reported outcomes

GP-level self-reported outcomes include beliefs about pain and impairment [53, 54], GP confidence [55] and reported clinical behaviour [56] (Additional file 5).

#### GP objective outcomes

GP-level objective outcomes will be GP consultation content recorded from EMR consultation notes by the research nurse immediately after consults and patient report of GP behaviour.

#### GP process measures

To examine the mechanisms by which FREE might impact GP behaviour, we will collect measures related to GP learning [57], satisfaction with training, treatment fidelity and proposed mechanisms of impact (Additional file 5) [58]. Intervention group GPs will record the number of FREE consultations they conduct during the experiential learning period. Associations between consultation count and GP knowledge, beliefs, behaviour, confidence and patient outcome will be analysed to explore whether a minimum number of training consultations is required to become competent in the approach.

Consultation recordings will be analysed to explore whether FREE consultations are longer than usual care LBP consultations. One consultation recording will be randomly selected from each GP with audio recordings available for content and thematic analysis. All consultations selected will be analysed using the Consult Audio Recording Checklist. The researcher conducting this analysis will be blind to group allocation.

### Data management

Study data will be collected and managed using REDCap (Research Electronic Data Capture) tools hosted at the University of Otago [59]. REDCap is a secure, web-based application designed to support data capture for research studies.

### Statistical analysis

Statistical significance will be judged with an α of 0.05. All results will be reported as estimates of effect size (e.g., mean difference, risk ratio, number needed to treat [NNT]) with 95% CI. All analyses will be conducted on an intention-to-treat basis.

Analyses will also account for clustering of data as appropriate. For the patient-level outcomes, this clustering will be specified at the GP level using random effects specifying the GP. Whereas randomisation is at the practice level, clustering effects on outcome values are expected to be driven mostly by inter-practitioner variability. For the GP-level outcomes, clustering will be specified at the practice level. The stratified randomisation will be handled by including the practice size stratum identifier in analytical models (less than or equal to eight FTE GPs, more than eight FTE GPs).

In most instances, analysis will be conducted using linear mixed models (for continuous numerical outcomes such as the RMDQ) or generalised linear mixed models (for categorical outcomes such as satisfaction levels). These models allow for inclusion of data from between baseline and the final endpoint to better estimate the differences at the main endpoint in the presence of missing follow-up data [60]. These models will be adjusted for important baseline covariates (age, sex, socioeconomic status, current back pain duration and nature [constant or episodic], receipt of recent or ongoing non-GP health care for back pain, previous history of back pain, baseline disability and baseline psychological factors [pain self-efficacy and recovery expectations]) [61]. The analysis will also be adjusted for baseline Health Care Providers’ Pain and Impairment Relationship Scale (HC-PAIRS) scores as measured at the level of the GP (as a measure of baseline treatment competence). We will analyse categorical outcomes using generalised linear mixed models (conditional treatment estimates) and generalised estimating equations (marginal treatment estimates) for each outcome: The former approach is to be considered the primary analysis for that output because the conditional treatment effect estimates relate to expected gains for each patient [60, 62].

For the primary outcome, we will report the relative risk (RR) of a 30% improvement in RMDQ score along with the NNT to achieve this target [63]. As a sensitivity analysis, the NNT and RR of a 2.5-point absolute reduction in RMDQ score will also be reported (in line with the absolute effect size stipulated for the primary outcome).

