## Methods/design

### Aim

The primary objective of the Low Back Pain in General Practice (LBPinGP) Study is to measure the effectiveness of the FREE approach versus usual care for LBP in terms of reduction in back-related functional impairment. Secondary objectives are to (1) measure the effectiveness of the FREE approach versus usual care for LBP in terms of reduction in pain and increase in health-related quality of life and patient satisfaction; (2) measure the cost-effectiveness of the FREE approach and usual care over a period of 6 months from societal, health system and Accident Compensation Corporation (ACC; a New Zealand government controlled universal accident insurance scheme) perspectives; and (3) consider which elements of the intervention mediate any observed changes in health outcomes. In sensitivity analysis, we will explore these same outcomes for new episodes of acute LBP (defined as less than 6 weeks’ duration with no LBP-related care received during the preceding 3 months) to explore the study’s initial hypothesis that FREE will be most effective when received at the first consultation for an episode of acute LBP.

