### Patient cost-utility analysis

By performing a cost-utility analysis, we will estimate the mean incremental cost per quality-adjusted life-year (QALY) gained (with QALYs to be calculated with the NZ EQ-5D Tariff 2, as recommended by the New Zealand Pharmaceutical Management Agency [64, 65]) from health care system, ACC and societal perspectives. Reference costs will be assigned for (1) all health care items to allow direct comparison and decrease patient recall requirements, (2) paid work (based on the mean income for someone of the participant's age and gender) to avoid data being skewed by participants with high income and to make results more generalisable to the general population, and (3) unpaid/voluntary work (based upon the minimum wage). The human capital approach will be used for work loss. Because each patient will be followed for 6 months, discounting will not be necessary.

We will report the incremental cost-effectiveness ratio and the monetary incremental net benefit with 95% CI around the estimates. Bootstrapped data will be displayed on a cost-effectiveness plane, and cost-effectiveness acceptability curves will be calculated to determine the likelihood that FREE will be considered cost-effective using one, two and three times gross domestic product per capita as policy-relevant willingness-to-pay thresholds. We will report results from sensitivity analyses by varying inputs over a range of feasible estimates for costs or effects of important variables that are likely to have wide variability (e.g., between small towns and large cities, or chance variability introduced by large costs in a single individual in one group).

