### Sample size

For 80% power to detect a between-group difference of 2.5 RMDQ points (the minimal clinically important difference) at 6 months, assuming SD of 6.0 [67] at a *p* value < 0.05 significance level, an individually randomised trial would require 91 patients per group. This has been inflated to 110 patients per group after adjustment for GP cluster effects (assuming a GP intra-cluster correlation coefficient at a conservative 0.05 and, on average, five patients per GP completing the trial). We aim to recruit 275 patient participants to allow for 20% loss to follow-up.

This design requires 22 GPs per study arm. To account for potential zero recruitment by some GPs, we will recruit 30 GPs per study arm. To further account for patient loss to follow-up (assumed ~ 20% of patients per GP) we will ask GPs to recruit seven patients. This gives a maximal potential sample size of 210 patients per study arm if all GPs recruit an average of 7 patients (total sample size = 60 GPs, 420 patients). Sample size calculations were performed using Stata 12 software (StataCorp, College Station, TX, USA).

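### The single covariate list for patient outcomes leaves pain (NPRS) and EQ-5D unadjusted for their own baseline values

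*Protocol article*

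**What the plan says.** In the protocol article, Statistical analysis, mixed models are the method for most patient outcomes, continuous and categorical. One sentence then adjusts these models for an enumerated set: age, sex, socioeconomic status, duration and nature of the back pain, non-GP care, previous back pain, and finally "baseline disability and baseline psychological factors [pain self-efficacy and recovery expectations". The GP's baseline HC-PAIRS score is added in the next sentence. The only baseline measure of symptom severity or function on the list is disability.

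The Aim section frames the first secondary objective as "reduction in pain and increase in health-related quality of life and patient satisfaction". The section on patient self-reported outcomes names the NPRS and EQ-5D as the measures for two of three core outcome domains.

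Two other sections bear on the point. Patient-reported process measures says that measures of pain and psychosocial function are collected partly as covariates for the main outcome analysis, and leaves their listing to an additional file. Patient cost-utility analysis says "we will estimate the mean incremental cost per quality-adjusted life-year (QALY) gained" and states no covariates.

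**The concern.** The list suits the RMDQ, because baseline disability is the outcome's own baseline domain. Applied unchanged to pain and EQ-5D, it leaves out what is usually the strongest single predictor of each. An analyst who follows the sentence literally would fit the pain model without baseline pain and the EQ-5D model without baseline EQ-5D, although both objectives are worded as change.

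The design makes this more than a formality. Up to ten practices are randomised, stratified only by practice size, and patients are recruited afterwards. With so few randomised units, the arms can differ by chance in baseline pain or quality of life. What is at stake is the precision of two important secondary results, and how far they can be moved by such a chance difference.

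**Working it through.** **The plan's own figure.** Inputs from Sample size and Statistical analysis: "For 80% power to detect a between-group difference of 2.5 RMDQ points (the minimal clinically important difference) at 6 months", "assuming SD of 6.0", "Statistical significance will be judged with an α of 0.05" (taken as two-sided), and "assuming a GP intra-cluster correlation coefficient at a conservative 0.05 and, on average, five patients per GP completing the trial".

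- Individually randomised: n = 2 × [6.0 × (1.960 + 0.842) / 2.5]² = 90.4, so 91 per group. This agrees with "an individually randomised trial would require 91 patients per group".
- Design effect: 1 + (5 − 1) × 0.05 = 1.2. Then 91 × 1.2 = 109.2, rounded up to 22 GPs × 5 = 110 per group.
- Dropout: 220 / 0.80 = 275.

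The figures reproduce. They concern the RMDQ only and take no credit for baseline adjustment, so this point does not change them.

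**Gain from adding the own baseline.** The documents give no correlations, so these ranges are assumptions:

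- a, baseline disability with the follow-up outcome: 0.2–0.4
- b, own baseline with the follow-up outcome: 0.3–0.6
- c, the two baselines with each other: 0.3–0.7

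Residual variance with disability only is 1 − a². With both it is 1 − R², where R² = (a² + b² − 2abc) / (1 − c²).

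| Case (a, b, c) | 1 − a² | 1 − R² | Ratio | Fall in SE |
|---|---|---|---|---|
| Smallest gain (0.4, 0.3, 0.7) | 0.840 | 0.839 | 0.999 | 0% |
| Mid values (0.3, 0.5, 0.5) | 0.910 | 0.747 | 0.821 | 9% |
| Largest gain (0.2, 0.6, 0.7) | 0.960 | 0.545 | 0.568 | 25% |

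At mid values 110 × 0.821 = 90.3, so about 91 patients per arm would give the precision that 110 give without the own baseline.

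**Size of a chance baseline difference.** In baseline SD units, with 110 completers per arm, SE = √(2 × DE / 110).

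- With the plan's GP-level design effect of 1.2: 0.148.
- With five practices per arm there are 110 / 5 = 22 completers per practice. An assumed practice ICC of 0.02 gives DE = 1 + 21 × 0.02 = 1.42 and SE 0.161. An ICC of 0.05 gives DE = 1 + 21 × 0.05 = 2.05 and SE 0.193.

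Under a normal approximation, an imbalance of at least 0.3 SD in either direction has probability about 4% at SE 0.148, 6% at 0.161 and 12% at 0.193.

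**Part that reaches the effect estimate.** Disability is already in the model, so only the part of the imbalance not explained by disability matters. Its SD is [(b − ac) / (1 − c²)] × √(1 − c²) × √(2 × DE / 110).

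- Mid values, DE 1.2: (0.35 / 0.75) × 0.866 × 0.148 = 0.060 outcome SD.
- Range over the assumed correlations, DE 1.2: 0.004 to 0.095.
- Mid values with the practice-level design effects: 0.060 × √(1.42 / 1.2) = 0.065 and 0.060 × √(2.05 / 1.2) = 0.078.

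The 9% and the 0.06 are one loss seen in two ways and must not be added. At DE 1.2, √[(2 × 1.2 / 110) × (0.910 − 0.747)] = 0.060.

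**The case against.** The strongest reply is that an omission is not an exclusion. The article condenses a fuller protocol, no analysis plan is at hand, and outcome-specific covariates are often settled there. The process-measures section also points to pain-related covariates beyond the printed list. This stands in part: the sponsor may already intend the adjustment. But the article is not silent here. It states an enumerated list and applies it to these models generally. The further covariates mentioned under process measures are for the main outcome analysis, so they do not supply an own baseline for the NPRS or EQ-5D. The sentence about using data between baseline and the final endpoint explains the use of interim follow-up. It does not say that baseline is modelled as a response.

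Several stronger readings are tempting, and the documents do not support them.

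- *All patient outcomes are affected.* They are not. The RMDQ has its own baseline domain on the list, and satisfaction may have no baseline.
- *The list leaves the QALY result unadjusted.* The cost-utility analysis is a separate section that states no covariates, and a detailed economic publication is planned. Silence there is not an error in the quoted list.
- *GP outcomes are all adjusted for their own baseline, so the plan is inconsistent.* The GP outcomes section says this only for the two vignette analyses.
- *A chance imbalance passes in full into the effect.* Disability adjustment removes part of it, and duration, self-efficacy and expectations may remove more.

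It also stands that collection of the NPRS and EQ-5D at baseline is an inference, because the patient schedule figure is not shown.

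**Conclusion.** The point holds for pain and EQ-5D, both secondary. Following the Statistical analysis section as written would analyse them without their own baseline. Randomisation still protects against systematic bias. The cost is lost precision and sensitivity to chance imbalance.

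The size rests on assumed correlations: 0–25% of the standard error, about 9% at mid values. At the plan's design effect of 1.2, the imbalance carried into the effect has SD about 0.06 outcome SD (range 0.004–0.095). It is somewhat larger if outcomes also cluster by practice. For scale, the RMDQ difference the trial is powered for is 2.5 / 6.0 = 0.42 SD.

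The primary analysis and the sample size of 91, 110 and 275 stand. The one proviso is that baseline disability must mean the RMDQ. The article does not name the instrument, and the patient schedule's abbreviations also include a Numeric Disability Rating Scale.

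**What to change.** In Statistical analysis:

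1. Add to the covariate list: *and the baseline value of the outcome being analysed, where collected*. The qualifier covers outcomes such as satisfaction that may have no baseline.
2. Name the instrument meant by baseline disability.
3. Reconcile the list with Patient-reported process measures, so that it is clear which pain and psychosocial measures are covariates and for which outcomes.

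As a companion step in Patient cost-utility analysis, state whether incremental QALYs are adjusted for baseline utility. Regression including baseline EQ-5D utility would be a sound choice.

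The cost is a clause or two, settled before the results are unblinded. If the NPRS and EQ-5D are in the baseline survey, no new data are needed, and the sample size does not change.
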